#### Anxiety and Depression

Anxiety and depressive symptoms will be measured at T1 to T3 using the Patient-Reported Outcomes Measurement Information System (PROMIS) [50,51] via brief computer adaptive tests (CATs). With CATs, participants’ responses guide the system’s choice of subsequent items from a bank of 29 items for anxiety and 28 items for depression.

#### Fear of Cancer Recurrence

At T1 to T3, participants will complete the Concerns About Recurrence Scale to assess fears about breast cancer recurrence [52]. Items address numerous life domains that could be impacted by a breast cancer recurrence, such as physical health and relationships. Participants are asked to use a 5-point response scale to indicate the extent to which they felt threatened by a recurrence in each domain.

#### Physical Activity

Physical activity will be measured at T1 to T3 using the International Physical Activity Questionnaire (IPAQ)-short form [53,54]. This measure consists of 7 items that assess physical activity over the past 7 days, and participants record the number of days per week or minutes per day spent doing specific activities. Previous reviews have demonstrated that the IPAQ-short form has high reliability [55,56], and the test-retest reliability of the questionnaire was at an acceptable level [55].

#### Dietary Intake

Dietary intake will be measured at T1 to T3 using the Brief Dietary Assessment Tool for Latinas [57]. This screening tool assesses fruit, vegetable, and fat intake over the past month.

#### Self-Efficacy

A total of 3 self-report questionnaires will be used to measure cancer-relevant self-efficacy at T1 to T3. First, the Communication and Attitudinal Self-Efficacy scale for cancer (CASE-cancer) is a psychometrically valid 12-item measure. A total of 2 CASE-cancer subscales will be used to assess a person with cancer’s self-efficacy in communication and information seeking [58]. Participants rate their level of confidence related to 12 skills using a 4-point response scale. This measure has been previously used with Latina BCSs [58,59]. Second, the PROMIS Self-Efficacy for Managing Emotions CAT will be administered, which assesses a person’s level of confidence to (1) manage symptoms of anger, anxiety, depression, disappointment, discouragement, frustration, and helplessness and (2) prevent symptoms from interfering with daily activities [60]. This measure has an item bank of 25 items. Finally, the 3-item “Assertiveness” scale from the Measure of Current Status will be used to assess a participant’s degree of confidence about asking and expressing their needs [61]. 

#### Breast Cancer Treatment Knowledge

The Knowledge about Breast Cancer questionnaire will be used to assess knowledge related to treatment at T1 to T3. This scale consists of 16 true or false statements regarding general breast cancer knowledge. The average number of correct responses will be calculated. This questionnaire was previously tested with a large sample of Spanish-speaking Latina BCSs [62] and used in the initial *My Guide* pilot study [10].

#### Cancer-Specific Distress

The Impact of Events Scale will be used to assess cancer-specific distress at T1 to T3. This measure comprises 2 subscales assessing the frequency of intrusive thoughts and avoidance following a stressful event [63,64].

### Analytic Plan

Descriptive statistics will be used to characterize the overall sample, each condition, and study acceptability and demand. To examine preliminary differences in feasibility between study conditions, we will use the chi-square test, Fisher exact test, and nonparametric Mann-Whitney *U* test for non-normal data, as appropriate. With 30 participants per study condition, there will be 80% power to detect approximately one-half SDs, assuming a 2-tailed test and a type I error rate of 5%. All power calculations were run using PROC POWER in SAS version 9.4.

For each study outcome, average changes from pre intervention to post intervention will be calculated via means (SD) and 95% CIs, and the mean changes within study condition will be converted to effect sizes. An analysis of covariance approach will be used to examine differences between the intervention and control conditions in follow-up scores, after adjusting for baseline score. Established cut-offs will also be referenced for clinically meaningful differences for the FACT-B and FACT-B subscales to identify ranges and patterns of changes in scores across conditions from baseline to follow-up.

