### Participants

Participants will be 60 Latina women who have been diagnosed with stage I-IIIA breast cancer, have completed surgery (eg, mastectomy and lumpectomy), and are actively receiving adjuvant treatment for breast cancer (eg, chemotherapy, radiation, and biologic therapy). We will enroll participants from the Robert H. Lurie Comprehensive Cancer Center at Northwestern Memorial Hospital, the University of Illinois Health System, and various community-based support groups sponsored by ALAS-WINGS, a Chicago-based nonprofit organization for Latina breast cancer patients.

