### Randomization

Eligible participants who provide informed consent will be individually randomized using a 1:1 ratio to either the intervention condition (*My Guide for Breast Cancer Treatment*) or the control condition (enhanced usual care) for a total of 3 months.

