### Data Collection and Outcomes

Consistent with past research, the feasibility of *My Guide for Breast Cancer Treatment* intervention will be evaluated by assessing the acceptability and demand of the app [18]. Acceptability of the app will be assessed at T3 using a previously tested app satisfaction questionnaire [20] that measures the usefulness, satisfaction, learnability, and usability of *My Guide for Breast Cancer Treatment.* Above average scores will be considered acceptable. Demand will be measured with study recruitment, retention, and participant use of *My Guide for Breast Cancer Treatment* (eg, frequency of log-ins, time spent using the app, and content accessed). Recruitment and retention rates of 70% or more will be considered acceptable based on our prior work and published studies [20,41,42].

All measures will be administered in each participant’s preferred language. For assessments completed in Spanish, we will use measures that have either been previously translated to Spanish and validated or measures that were translated to Spanish for this study by IRB-approved translators.

Participants will complete a self-report sociodemographic questionnaire at T1 including questions related to age, racial background, Latina ancestry, income, employment, relationship status, educational attainment, years living in the United States, and subjective social status using the MacArthur scale [43]. Participants will self-report clinical information including time since breast cancer diagnosis and surgery, stage of diagnosis, type of surgery, current treatment regimen (eg, chemotherapy and radiation), additional medications, medical comorbidities (assessed using the Charlson Comorbidity Index [44]), and past or current psychiatric diagnoses. Financial toxicity will be measured using Comprehensive Score for financial Toxicity-Functional Assessment of Chronic Illness Therapy [45]. All self-reported medical- and disease-related information will be verified via medical chart review.

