### Future Directions

There are several areas for future directions. If found feasible, future studies should establish the efficacy of *My Guide for Breast Cancer Treatment* across a nation-wide, heterogeneous sample of Latina women diagnosed with breast cancer. Currently, the *My Guide for Breast Cancer Treatment* app does not include any social media aspects; the potential benefit of adding a social media component to *My Guide for Breast Cancer Treatment* may be another important direction for future iterations of the app. In addition, given the multiple components of this feasibility trial (ie, app, telecoaching, and SMS text messaging), another important future direction will be to disentangle the effects of each component of the intervention on study outcomes.

Findings from this second study of the *My Guide for Breast Cancer Treatment* app are expected to contribute to the literature by establishing the efficacy of a smartphone-delivered intervention to enhance self-management during breast cancer treatment for improving HRQoL and symptom burden among Latina patients. Given the technology-based delivery of this app, the *My Guide for Breast Cancer Treatment* app has the potential for nation-wide scalability and therefore can increase access to supportive care resources among Latina breast cancer patients.

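### The stated 80% power for about half an SD with 30 per arm does not hold between arms: unadjusted power is 48% and the detectable difference is 0.74 SD before dropout

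*Protocol article*

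**What the plan says.** All references are to the protocol article.

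- **Sample and allocation.** Participants: "Participants will be 60 Latina women". Randomization: "individually randomized using a 1:1 ratio".
- **Power.** Analytic Plan: "With 30 participants per study condition, there will be 80% power to detect approximately one-half SDs", for a two-tailed test at 5%. The software is named (PROC POWER), but not the test, the SD scale, a baseline-to-follow-up correlation or a dropout allowance. The sentence directly follows one on differences between the study conditions.
- **Outcome analysis.** The next paragraph of the Analytic Plan plans two things: within-condition mean changes expressed as effect sizes, and a between-condition ANCOVA of follow-up scores adjusted for baseline.
- **Hypothesis.** The Hypotheses section expects better outcomes in the app arm than under enhanced usual care, which is a between-arm question.
- **Retention.** Data Collection and Outcomes: "Recruitment and retention rates of 70% or more will be considered acceptable".
- **Efficacy.** Future Directions expects the findings to "contribute to the literature by establishing the efficacy of a smartphone-delivered intervention", although the same section leaves establishing efficacy to later studies if the app proves feasible.

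**The concern.** Thirty per arm is far fewer than a half-SD difference between two groups usually requires, and the sentence gives no device, such as a stated correlation, that would close the gap. It is the only quantitative support for the sample size.

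If the figure is wrong, a reader who trusts it could take a non-significant between-arm result as evidence against a half-SD benefit that the trial had a large chance of missing. Anyone sizing the follow-on study could carry the same error forward. The Discussion's wording on efficacy would also go beyond what the design can support.

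**Working it through.** **Inputs from the protocol:** n = 30 per arm (Analytic Plan; 60 women, 1:1), effect d = 0.5 SD, two-sided 5%, target power 80%. Retention of 70% gives 0.70 × 30 = 21 per arm.

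**Assumed, because not stated:** baseline-to-follow-up correlation r, shown over 0.3 to 0.7.

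**1. Trying to reproduce 80% as a two-arm comparison.** Two-sample t-test, noncentral t, df = 2n − 2 = 58, noncentrality = d × √(n/2).
- Noncentrality = 0.5 × √15 = 1.936; critical value 2.002.
- Power = **47.8%** (normal approximation 49.1%).
- Detectable difference at 80% power = **0.736 SD** (normal approximation (1.960 + 0.842) × √(2/30) = 0.723).
- For 80% power at 0.5 SD: **64 per arm** (normal approximation 63).
- A one-sided test gives 60.6%. A Mann-Whitney test, taken at relative efficiency 3/π, gives about 46%.

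None of these gives 80%.

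**2. What does come near the figure.** One-sample (paired) t-test within one arm, n = 30, df = 29, noncentrality = d × √n = 0.5 × √30 = 2.739.
- Power at 0.5 SD = 75.4%.
- Detectable effect at 80% power = **0.529 SD**, in SDs of the change score.

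This is the only test tried that lands near the printed figure without an added assumption. That it is the source is an inference; the protocol does not say.

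**3. The planned ANCOVA.** The residual SD is the score SD × √(1 − r²), so the effect becomes 0.5/√(1 − r²), with df = 2n − 3. Example at r = 0.6: √(1 − 0.36) = 0.8, and 0.5/0.8 = 0.625.

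| r | Power at 0.5 SD, 30 per arm | Detectable at 80%, 30 per arm | Power at 0.5 SD, 21 per arm | Detectable at 80%, 21 per arm |
|---|---|---|---|---|
| unadjusted | 48% | 0.74 SD | 35% | 0.89 SD |
| 0.3 | 51% | 0.70 SD | 38% | 0.85 SD |
| 0.5 | 59% | 0.64 SD | 45% | 0.77 SD |
| 0.6 | 66% | 0.59 SD | 51% | 0.71 SD |
| 0.7 | 76% | 0.53 SD | 60% | 0.63 SD |

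For 80% power at 0.5 SD, r must be about **0.73** with 30 per arm or about **0.83** with 21 per arm.

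**4. Precision.** The 95% CI half-width for an unadjusted difference is t × √(2/n).
- 30 per arm: 2.002 × √(2/30) = **0.52 SD**.
- 21 per arm: 2.021 × √(2/21) = **0.62 SD**.

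**The case against.** - **The outcome analysis is ANCOVA, so 48% is only the floor.** This is right. At r = 0.7 the chance of missing a half-SD effect is about 24%, not one half. If the word for approximately is read to allow 0.53 SD, as the paired calculation needs, ANCOVA with all 60 followed gets there at r of about 0.7. But no r is given, so the printed 80% cannot be recovered from the document, and at r = 0.5 or 0.6 it still fails clearly.
- **The figure may be a correct within-condition calculation, poorly labelled.** This is possible, since within-condition effect sizes are planned. But the sentence follows one about differences between conditions and does not say it means something else. Change within an arm during adjuvant treatment cannot separate the app's effect from the course of treatment. On this reading the between-arm hypothesis has no power statement at all.
- **The 70% retention figure is a feasibility threshold, not a forecast.** This is true. The 21-per-arm results show the lower end of what the protocol would accept, not what it expects.
- **This is a feasibility trial whose efficacy aim is called preliminary, and no decision rule rests on a p-value.** This is also true, and it is why no larger sample is asked for. It does not make the printed figure correct.
- **An article may leave details to the full protocol.** The point is not an omission. A printed figure does not fit the comparison it accompanies.

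**Conclusion.** The concern holds. With the stated inputs, a two-arm comparison of 30 per arm has 48% power at 0.5 SD and a detectable difference of 0.74 SD, not 80% and about 0.5 SD. These values assume an unadjusted t-test and complete follow-up.

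For the planned ANCOVA the shortfall depends on the unstated correlation: moderate at r = 0.7, large at 0.5, and gone only from about 0.73 upward without loss. Retention at the accepted minimum makes every figure worse. The Discussion's phrase on establishing efficacy is a separate inconsistency of wording, but it points the same way and should be corrected together with the power sentence.

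This must be corrected because it is the protocol's only sample-size justification.

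**What to change.** Keep 60 participants and correct the text.

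1. **Analytic Plan: name the test and the SD scale, and replace the power sentence.** Suggested text: *With 30 per arm (two-sided 5%), a between-arm comparison has 80% power for a difference of 0.74 SD unadjusted, or about 0.59 SD by ANCOVA if the baseline-to-follow-up correlation is 0.6. With 70% retention (21 per arm) the values are 0.89 SD and about 0.71 SD.* Mark the correlation as an assumption.
2. **If the printed figure was a within-condition calculation,** label it as such, in SDs of change (0.53 SD with n = 30), and give the between-arm figure beside it.
3. **Add the expected precision:** an unadjusted 95% CI half-width of 0.52 SD with 30 per arm, or 0.62 SD with 21.
4. **State that between-arm estimates are preliminary** and that non-significance is not evidence of no effect.
5. **Future Directions:** replace the phrase on establishing efficacy with *providing preliminary estimates of efficacy*.

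The cost is wording only; sample, design, conduct and analysis are unchanged. The stated power becomes less favourable.

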Study outcomes and intervention targets will be measured at study enrollment and before randomization (T1), 6 weeks postbaseline (T2), and 12 weeks postbaseline (T3). All assessment time points will consist of measures assessing our primary outcomes, intervention targets, and secondary outcomes. In addition, all participants will complete a sociodemographic questionnaire at T1, and participants randomized to the intervention condition will be asked to complete an exit survey at T3. Assessments are estimated to take approximately 35 min to complete. Participants randomized to the intervention condition will also be asked to complete brief, 3-min, weekly questionnaires throughout the course of the 12-week intervention. See section *Data Collection and Outcomes* for greater detail. Participants will be compensated US $100 for their participation in the study and receive partial reimbursement for telephone data usage plans. Participants without an internet-enabled device will be provided one for the duration of the study. All study procedures and assessments have been approved by the institutional review board (IRB) of record for this multisite study (Northwestern IRB).

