#### Health-Related Quality of Life

At T1 to T3, participants will complete the Functional Assessment of Cancer Therapy-Breast (FACT-B). The FACT-B has been extensively used among breast cancer patients [46,47] and measures physical, emotional, social, and functional well-being, as well as breast cancer–related concerns over the past 7 days using a 5-point response scale [46]. Participants randomized to the *My Guide for Breast Cancer Treatment* intervention condition will also complete the rapid version of the Functional Assessment of Cancer Therapy-General (FACT-G7) on their smartphones every week throughout the 12-week intervention. The FACT-G7 assesses the most prominent HRQoL concerns among cancer patients and is both valid and reliable [48]. The FACT-G7 takes approximately 5 min to complete and is therefore an ideal brief measure of HRQoL to include in a smartphone-delivered intervention.

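### The 12-week ANCOVA leaves out 6-week scores already collected from women lost later; a joint model of both follow-ups would use them and guard against dropout that differs by arm

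*Protocol article*

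**What the plan says.** The Study Design section has outcomes "measured at study enrollment and before randomization (T1), 6 weeks postbaseline (T2), and 12 weeks postbaseline (T3"). The outcome sections repeat this schedule for each instrument; for the main quality-of-life measure, "At T1 to T3, participants will complete the Functional Assessment of Cancer Therapy-Breast (FACT-B").

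The Analytic Plan gives a single between-arm method: "An analysis of covariance approach will be used to examine differences between the intervention and control conditions in follow-up scores", with adjustment for the baseline score. It names no repeated-measures model and does not say which follow-up is the main contrast.

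On loss to follow-up, Data Collection and Outcomes states: "Recruitment and retention rates of 70% or more will be considered acceptable based on our prior work and published studies". The Participants section sets the sample at 60, allocated 1:1. Study Design stratifies randomization by recruitment site and language.

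**The concern.** An ANCOVA of the T3 score on the baseline score needs a T3 score. A woman with T1 and T2 but no T3 adds nothing to the 12-week comparison, although her T2 score is probably the best available predictor of the missing value. In a trial of 60, information that has been paid for goes unused.

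The arms also differ in ways that could affect who stays. The app arm is asked for 1.5 hours of use a week, a short weekly questionnaire and a two-weekly concerns questionnaire, with a telecoaching call in any week of low use. Controls have none of this, and they receive the app once they have completed T3. If women whose 6-week scores are poor leave one arm more readily than the other, the completers are no longer comparable at T3. Baseline adjustment does not repair that.

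**Working it through.** **Inputs from the protocol.** 60 women, 30 per arm; outcomes at T1, T2 and T3; baseline-adjusted ANCOVA; retention of at least 70% acceptable. The largest loss compatible with that criterion is 60 × 0.30 = 18, leaving 42, or 21 per arm if evenly spread. The plan gives no figure for bias or for the effect of missing data, so there is none to reproduce. Its power statement (80% for about 0.5 SD) is a separate matter. It does not reproduce for an unadjusted two-sample t-test with 30 per arm, which has about 48% power, but nothing here depends on it.

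**Assumptions not in the protocol.** Correlations T1–T2 0.65, T1–T3 0.60 and T2–T3 0.70; unit SD; logistic dropout after T2 in which women with worse T2 scores leave more often.

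**Precision under random dropout.** The squared partial correlation of T2 and T3 given T1 is

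(0.70 − 0.65 × 0.60)² / [(1 − 0.65²)(1 − 0.60²)] = 0.0961 / 0.3696 = 0.26.

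If every lost woman was seen at T2, the ratio of the T3 contrast's variance (joint model to ANCOVA) is 1 − (fraction lost) × 0.26:

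- 70% retained: 1 − 0.30 × 0.26 = 0.922, a gain of about 8%.
- 80% retained: 1 − 0.20 × 0.26 = 0.948, a gain of about 5%.
- If half the losses come before T2, the gains fall to about 5% and 3%.

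**Bias.** With no true effect, the ANCOVA bias is roughly the slope of T3 on T2 given T1, (0.70 − 0.39) / (1 − 0.4225) = 0.54, times the arm difference in baseline-adjusted T2 among the women retained. If selection is alike in both arms, that difference is zero. Large-sample simulation, no true effect, 70% retained in each arm:

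| Dropout after T2 | ANCOVA bias (SD) | With T2 used |
|---|---|---|
| App arm only, log-odds slope 0.5 / 1.0 / 1.5 per SD | 0.04 / 0.08 / 0.10 | about 0 |
| Same, but half the losses at random before T2 | 0.03 / 0.05 / 0.06–0.07 | about 0 |
| Slope 1.0 in the app arm, 0.5 in the control arm | about 0.04 | about 0 |
| Slope 1.0 in both arms | about 0 | about 0 |

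A second set of runs used correlations of 0.6 (T1–T2), 0.5 (T1–T3) and 0.6 (T2–T3), with slope 1 unless stated:

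- T2-driven dropout in the app arm only: +0.08. In the control arm only: −0.08.
- Same slope in both arms, but control/app retention of 80/60 or 90/50: +0.05 or +0.10.
- One common T2 rule with a true effect of 0.5 SD, so that retention differs because the arms differ: −0.02 (slope 1) to −0.05 (slope 2).
- Dropout driven by baseline alone: about 0.
- Using T2 brings the bias to about 0 in all of these.
- Dropout driven by the unobserved T3 score in one arm only: 0.20 with ANCOVA, still 0.16 with T2 used.

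**Size against noise.** With 21 per arm and a baseline correlation of 0.60, the standard error is √(2/21) × √(1 − 0.36) = 0.309 × 0.80 = 0.25 SD. A bias of 0.04 to 0.10 SD is 0.16 to 0.40 of a standard error. By normal approximation it moves the two-sided type I error from 5% to about 5.3 to 6.9%.

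**The case against.** A reader might infer that the T3 contrast is biased whenever women who are doing worse leave. The documents and the arithmetic do not support that. If T2-related dropout has the same strength and leaves the same retention in both arms, the bias is about zero, and dropout explained by baseline is already covered by the planned adjustment.

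A reader might also infer that the bias must favour the app. The protocol gives reasons in both directions. The app arm carries more burden, but it also has regular contact through telecoaching calls or text messages. Compensation, data-plan reimbursement and loaned devices are described for participants generally. Stopping app use is not the same as missing the T3 questionnaire.

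Other objections also stand. The protocol does not say that the ANCOVAs are separate or restricted to completers; that is the ordinary meaning of the method named. A full protocol or SAP, not shown, could add imputation using T2, which would meet the point. The absence of missing-data rules from the article is therefore not the complaint. The 70% figure is a feasibility threshold and not an expected rate. The upper bias figures rest on a favourable case, with one-arm dropout and T2 seen for every woman lost. The trial's aims are preliminary, and the bias is small against its sampling error.

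None of this shows that the stated method does as well as one that uses T2. It limits the size and certainty of the gain.

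**Conclusion.** The point holds as a cheap improvement to a legitimate but less efficient analysis. As written, the T3 contrast ignores T2 scores from women lost afterwards, and it relies on dropout being unrelated to T3 given arm and baseline alone. Bias arises only if T2-related dropout differs by arm or leaves unequal retention, and its direction cannot be told in advance. Its size is about 0.04 to 0.10 SD under the assumed correlations with 30% loss, one-arm dropout and T2 seen for every woman lost. That is 8 to 20% of the half-SD difference in the power statement, but less than half a standard error. It is smaller when some women leave before T2, and about zero when dropout is alike in both arms. The precision gain is at most about 5 to 8% of the variance.

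**What to change.** For each outcome, replace the ANCOVA of a single follow-up score with one likelihood-based repeated-measures model of T2 and T3. Include arm by visit, baseline score by visit, and the stratification factors site and language, with an unstructured covariance for the two visits. Analyse all women with any follow-up score in the arm to which they were randomized, and report the T3 contrast from this model. If ANCOVA is preferred, multiple imputation of T3 by arm, using T1 and T2, would serve the same end.

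No new data are needed. The cost is slightly more modelling and a few lines of text. The model relies on data being missing at random given baseline, T2 and arm, a weaker assumption than the ANCOVA's. It does not cure dropout that depends on unobserved T3 scores, and a woman with neither follow-up still contributes nothing. Retention at T2 and T3 should be reported by arm so that readers can judge whether the condition for bias arose.

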### Study Design

This RCT is designed to assess the preliminary feasibility and efficacy of the *My Guide for Breast Cancer Treatment* smartphone app for improving HRQoL and symptom burden in Latina women receiving treatment for primary breast cancer. After providing informed consent, participants will be randomized to the *My Guide for Breast Cancer Treatment* intervention condition or to the enhanced usual care control condition. Randomization will be stratified by recruitment site and language (ie, English and Spanish). Participants randomized to the *My Guide for Breast Cancer Treatment* intervention condition will have access to the smartphone app for 12 weeks and will be encouraged to use the app for 1.5 hours each week. The *My Guide for Breast Cancer Treatment* app is accessible on all smartphones (eg, Apple and Samsung) as well as tablets and computer websites. It is available in both English and Spanish, and participants will be provided the app in their preferred language. Participants randomized to the *My Guide for Breast Cancer Treatment* intervention condition will be oriented to the app and instructed to use it for 1.5 hours each week for a duration of 12 weeks. A 12-week intervention timeframe was selected based on previous studies indicating benefits in HRQoL and symptom burden outcomes after 10 weeks of behavioral interventions and the expected length of adjuvant treatments [19-21]. Thus, we believe that 12 weeks will allow sufficient time for participants to access and benefit from the *My Guide for Breast Cancer Treatment* app content. Intervention participants will also be assigned a bilingual telecoach for the duration of the study. Using a stepped-care approach [22], intervention participants will receive weekly telecoaching calls based on their level of adherence to the recommended app usage.

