### Eligibility

We will identify participants through screening of the electronic medical record (EMR), and final determinations for study eligibility will be made based on a self-report questionnaire via telephone interview. To be included in the study, participants must (1) be female, because male breast cancer patients represent less than 1% of the breast cancer cases; (2) have a diagnosis of stage I-IIIA breast cancer; (3) have completed surgery for breast cancer; (4) be within any timepoint of the adjuvant treatment trajectory for breast cancer (eg, chemotherapy, radiation, surgery, and biologic therapy); (5) be at least 18 years of age; (6) be able to speak and read English or Spanish; (7) be able to provide informed consent; and (8) self-identify as Hispanic/Latina ethnicity. Participants will be excluded from the study if they (1) have a hearing, motor, visual, or voice impairment that would preclude completion of study procedures; (2) have been diagnosed with a psychotic disorder, bipolar disorder, dissociative disorder, or any other diagnosis for which study participation would be inappropriate or dangerous; (3) endorse suicidal ideation, plan, or intent; (4) endorse illicit substance or alcohol dependence; or (5) have been diagnosed with dementia. Patients with metastatic disease will not be included in this study, as they have more extensive treatment regimens and substantially different needs relative to patients with earlier stages of breast cancer.

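### Randomization is stratified by recruitment site and language, but the stated ANCOVA adjusts for baseline score alone; if these factors are prognostic beyond baseline, the analysis is conservative and loses some power

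*Protocol article*

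**What the plan says.** Under Study Design the article states: "Randomization will be stratified by recruitment site and language (ie, English and Spanish". The Randomization section adds that women "will be individually randomized using a 1:1 ratio". The Participants section sets the total at 60 and names three recruitment sources: a comprehensive cancer center, a university health system, and community support groups run by one organization.

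The Analytic Plan examines "differences between the intervention and control conditions in follow-up scores, after adjusting for baseline score". No other covariate is named there, and no section of the article says that site or language enters the model. The same section states: "With 30 participants per study condition, there will be 80% power to detect approximately one-half SDs", two-sided at the 5% level. It gives no baseline-to-follow-up correlation and no assumed effect of the stratification factors.

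**The concern.** Stratified allocation makes the arms more alike on site and language than simple randomization would. The treatment estimate then varies less from one possible allocation to another, because chance imbalance on those factors has largely been removed. A model without the factors does not register this. Their variance stays in the residual, so the reported standard error exceeds the true one. Intervals come out too wide and the test falls below its nominal 5%.

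Precision is at stake, not validity. With 60 women there is little precision to spare, and part of what the stratified design provides would go unused. Some prognostic value is plausible: the recruitment sources are of different kinds, the introduction singles out primarily Spanish-speaking women as having particular unmet need, and the investigators chose to stratify on these two factors.

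**Working it through.** **Inputs from the document.** 30 per arm, 1:1 allocation, two-sided 5%, effect 0.5 SD, stratification by site and language, ANCOVA on baseline score.

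**Assumptions, not in the document.** Each of the three recruitment sources is a site stratum, which with two languages gives up to 6 strata. Allocation uses permuted blocks of 4 within stratum. The baseline-to-follow-up correlation ρ is 0.5 or 0.7. R² is the share of variance left after baseline that site and language explain.

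**Step 1: the plan's own figure.** For an unadjusted comparison, SE = √(2/30) = 0.258 SD and 0.5/0.258 = 1.94. Power is 49.1% by the normal approximation and 47.8% by the two-sample t-test. Reaching 80% needs 63 per arm, or a difference of 0.74 SD at 30 per arm. With baseline adjustment the residual SD is √(1 − ρ²), and 80% at 0.5 SD needs ρ of about 0.73, which is not stated. The 80% figure is therefore not reproduced from the stated inputs.

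**Step 2: the expected direction.** With perfect balance on the strata, the true SE of the baseline-only estimate is the reported SE × √(1 − R²). The actual two-sided error is then about 2 × [1 − Φ(1.96/√(1 − R²))]. At R² = 10% this is 2 × [1 − Φ(2.07)] = 3.9%. At 20% it is 2 × [1 − Φ(2.19)] = 2.8%. Incomplete blocks make real balance less than perfect, so the simulated error should lie slightly nearer 5%.

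**Step 3: simulation.** 6,000 trials per cell. Each arrow runs from baseline only to baseline + site + language.

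| R² | Type I error, ρ = 0.5 (%) | Power, ρ = 0.5 (%) | Type I error, ρ = 0.7 (%) | Power, ρ = 0.7 (%) |
|---|---|---|---|---|
| 0 | 5.0 → 5.2 | 57.9 → 57.5 | 5.2 → 5.3 | 75.0 → 74.5 |
| 5% | 4.8 → 5.4 | 60.0 → 61.5 | 4.6 → 5.1 | 76.0 → 77.2 |
| 10% | 4.2 → 5.3 | 58.9 → 62.7 | 4.1 → 5.0 | 75.9 → 79.2 |
| 20% | 3.1 → 5.2 | 58.9 → 67.2 | 3.1 → 5.1 | 77.1 → 83.3 |
| 30% | 2.0 → 4.8 | 60.0 → 74.0 | 2.0 → 4.5 | 78.0 → 88.3 |

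Monte Carlo error is about √(0.05 × 0.95/6000) = 0.3 points on type I error and about 0.6 points on each power.

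At ρ = 0.7 under the null, the baseline-only model reports a mean SE of 0.186. The actual SD of the estimate is 0.179 at R² = 10% and 0.171 at 20%. Intervals are therefore about 4% (0.186/0.179) and 9% (0.186/0.171) too wide. With the factors in the model at R² = 20%, the reported SE and actual SD agree (0.167 and 0.169).

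**Step 4: sensitivity.** Separate runs at ρ = 0.6 gave 64.5% → 64.7% at R² = 2% and 65.2% → 66.7% at 5%. A further set gave 66% → 69%, 67% → 74% and 67% → 80% at 10%, 20% and 30%. Block sizes of 4, 8 and 12 gave similar results.

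**Step 5: cost in degrees of freedom.** The baseline-only model leaves 60 − 3 = 57. Two site terms and one language term leave 54.

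**The case against.** The strongest objection is that the loss is conditional and may be small. The baseline value of the same scale already absorbs stable site and language differences, each woman is assessed in her preferred language, and the support resources listed are all in the Chicago area. If the factors explain only 0 to 2% of residual variance, adding them gains almost nothing. This stands. A reader might infer that the intervals are too wide and power is lost as a matter of fact, but the document gives no figure that supports an unconditional statement.

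A second objection is that the Analytic Plan is a summary: it does not say that baseline is the only covariate, and a full analysis plan could add the strata. That is possible. But the article does not leave the adjustment open; it names an adjustment variable, and that choice does not match the randomization it describes. The mismatch can fairly be raised on the text as it stands.

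Third, the trial is described as preliminary, and establishing efficacy is left to later studies, so a conservative test does limited harm. This also stands, and it keeps the point modest.

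A reader might also infer that treatment regimen at enrolment belongs in the model, because women may "be within any timepoint of the adjuvant treatment trajectory for breast cancer". The argument here does not reach that far. Regimen is not a stratification factor, its effect was not simulated, and the document gives no figure for it. Leaving a collected variable out of the model is not an error in a randomized trial.

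**Conclusion.** The concern holds in conditional form: the stated model omits the two factors on which allocation is stratified. If they are prognostic beyond baseline, the analysis is conservative. Simulated type I error is about 4% when they explain 10% of residual variance and about 3% at 20%. Adding them changes power at 0.5 SD by about -0.5 points at 0%, +1 at 5%, +3 to 4 at 10% and +6 to 8 at 20%. These figures rest on assumed correlations, stratum structure and R², and on all 60 women being analysed.

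Two stronger readings are not supported. A nominal 5% that is inexact might suggest a threat to validity, but the error is on the safe side: false positives are not inflated and the estimate is unbiased. Nor would the change rescue the claim that "there will be 80% power to detect approximately one-half SDs". In the simulations, adjusted power passes 80% only with ρ = 0.7 and R² of 20% or more, and the document states neither quantity.

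**What to change.** Amend the Analytic Plan so that, for each outcome, the ANCOVA is follow-up score = arm + baseline score + recruitment site + language. Enter site and language as main effects rather than as up to six site-by-language cells, which would be thinly filled with 60 women.

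The cost is one sentence and about 3 of 57 residual degrees of freedom, with at most about half a point of power lost if the strata predict nothing. If retention fell to the 70% that the article calls acceptable, 0.7 × 60 = 42 women would remain and residual degrees of freedom would go from 39 to 36; the simulations did not cover that case. The 80% power statement needs its own correction.
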